**Data Collection and Management**

*Staff training.* Staff will be trained to collect data utilizing good clinical practices, and monitors will ensure that that standard is adhered to. For assessments completed by two different individuals, mock assessments will be used to ensure that there is adequate agreement (the specific kappa level depends on the assessment).

*Data collection.* Data will be collected using paper-and-pen or direct computer entry and transcribed onto teleform data sheets. A trained research assistant will perform quality assurance monitoring of each subject’s file to assure that there are no variances in collection procedures over time and to assure completeness.

**Statistical Analysis**

*Power analysis.* The proposed sample size of 60 should allow detection of small-to-medium effects (approximately f=.17) when comparing conditions (within-subject factors) using repeated measures analyses with power=.80 and two-tailed alpha=.05. This effect size translates to a difference of approximately 1/3 standard deviation units (d=.33) in differences in means across conditions (Cohen 1988; Elashoff 2000). A moderate within-subject correlation of .5 was assumed across conditions. We have conservatively powered the study for 2-tailed tests to cover the range of primary and secondary hypotheses; however, since we expect disulfiram to reduce cocaine choices, power would be greater for a one-tailed test of the primary hypothesis in each experiment. This sample size will also allow for detecting medium-to-large effects in assessing secondary hypotheses (such as a linear trend in cocaine dose-response) with Bonferroni correction for post hoc comparisons. The above power analysis has been calculated assuming no order effects for disulfiram vs. placebo conditions; however, if order effects are detected, then analyses will assess effects within order conditions, with a corresponding decrease in power allowing detection of medium effect sizes (f=.26) across condition.

*Statistical Analysis.* Descriptive statistics will be used to summarize sample characteristics on all measures, as appropriate to measurement characteristics of individual variables. Order effects (for disulfiram vs placebo) will be assessed using repeated measures ANOVA to determine equivalence; because of random assignment, no differences are anticipated. However, if significant differences are found, then primary analyses will examine effects within each order condition.

Repeated measures ANOVA will be used to assess effects of disulfiram within each experiment. For each experiment, a general linear model will include within-subject factors representing condition (disulfiram vs. placebo) and cocaine dosage. Separate analyses will be conducted for each outcome measure. If outcome measures are substantially non-normal, then a GEE (generalized estimating equations) approach will be used for testing hypotheses instead of the general linear model for repeated measures (Burton et al 1998). This extended approach allows analysis of non-normally distributed data (e.g. binomial or gamma) as well as inclusion of a correlated covariance structure to accommodate within-subject effects.

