**Research Participants**

Each subject will complete procedures while receiving placebo and disulfiram. We anticipate that 75 volunteers will enter the study and that there will be a dropout rate of 20-30%, yielding a sample size of 60.

*Recruitment*

Potential participants will be recruited using flyers, print ads, and radio advertisements. Our experience from previous studies indicates that well-placed and maintained flyers coupled with print and radio spots are sufficient to maintain frequent calls to our toll-free number. Over a recent 12-month period, our recruitment center received approximately 2,600 calls from stimulant users interested in participating in our studies. From those contacts, approximately 10% of the callers were eligible to meet with our research staff for consultation. Roughly 20% of those callers attended an initial screening appointment and met general inclusion criteria for a non-treatment-seeking study involving cocaine or methamphetamine administration (fewer met stricter criteria for particular studies, as some studies require prior IV experience). Thus, our existing recruitment approach provided about 50 eligible participants per year. We can easily increase the intensity of recruitment efforts in to accommodate the recruitment needs of the proposed project.

Participants who call our toll-free number are informed about the *general* requirements of the study and appointments are scheduled for those who are interested. Participants are not informed about the specific inclusion/exclusion criteria in order to avoid participants tailoring their responses in order to enter the protocol. During a face-to-face interview with a study physician participants are given consent documents that are read to them if needed. Following completion of the informed consent process, participants are screened using the criteria below. At several times during the screening process, participants are informed that treatment is available and referrals are provided if desired. Following completion of the consent process, participants will an oral swab will be used to collect epithelial cells that will provide DNA for genotyping at the DBH locus. Subjects with all genotypes will be included in this study.

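### Sixty completers give about 71% two-tailed power for d=.33, not 80%, and 20–30% dropout from 75 entrants leaves 52 to 60 completers, not 60

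*Protocol*

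**What the plan says.** All the inputs are in the protocol.

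- **Power claim** (Statistical Analysis, power paragraph): "The proposed sample size of 60 should allow detection of small-to-medium effects (approximately f=.17) when comparing conditions", "using repeated measures analyses with power=.80 and two-tailed alpha=.05". The paragraph converts this f to a difference of about one third of a standard deviation, d=.33.
- **Correlation** (same paragraph): "A moderate within-subject correlation of .5 was assumed across conditions".
- **Sidedness** (same paragraph): "We have conservatively powered the study for 2-tailed tests to cover the range of primary and secondary hypotheses". It adds that a one-tailed test of the primary hypothesis would have more power.
- **Fallback if order effects are found** (same paragraph): analysis within each order, "allowing detection of medium effect sizes (f=.26) across condition".
- **Enrolment** (Research Participants): 75 are expected to enter, and "there will be a dropout rate of 20-30%, yielding a sample size of 60".
- **Contrast** (Experiments): the planned comparison for each measure is disulfiram against placebo, made separately at each cocaine dose. Every subject receives both conditions.

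**The concern.** The paragraph fixes sample size, alpha, sidedness, correlation and effect size, so the power follows from them and can be checked. A paired comparison of 60 subjects at a third of a standard deviation looked too small for .80. The dropout sentence gives a range of rates but a single yield, which matches only one end of that range.

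Both discrepancies make the trial look stronger than it is. A reader who relies on the protocol would believe that the trial had a one-in-five chance of missing a one-third SD effect, when the chance is closer to one in three. That matters when a non-significant result is set against the planned power. It also matters when judging whether 75 entrants are enough.

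**Working it through.** **Inputs.** n=60, two-tailed alpha .05, correlation .5, f≈.17, d≈.33 and a fallback f=.26 (Statistical Analysis); 75 entrants and 20–30% dropout (Research Participants); two conditions compared at each cocaine dose (Experiments).

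**Effect-size conversion.** For two condition means, f = d/2, so d=.33 is f=.165 and f=.17 is d=.34. The protocol's equation of f=.17 with d=.33 is this two-level conversion, up to rounding.

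**Paired effect size.** dz = d / √(2(1 − ρ)). With ρ=.5, dz = d / √1 = d.

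**Power.** A repeated-measures F test on a two-level factor is the paired t-test. Its noncentrality is dz·√n on n − 1 degrees of freedom. At n=60 and d=.33 this is .33 × √60 = 2.556, against a two-tailed critical value of 2.001 on 59 df.

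| Setting (ρ=.5) | Power |
|---|---|
| n=60, d=.33, two-tailed (as stated) | .710 |
| n=60, d=1/3, two-tailed | .719 |
| n=60, f=.17 (d=.34), two-tailed | .736 |
| n=60, d=.349 (largest f that rounds to .17), two-tailed | .758 |
| n=60, d=.33, one-tailed | .811 |
| n=75, d=.33, two-tailed | .805 |

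The stated .80 is not reproduced. The normal approximation does not close the gap: it gives .725 at d=.33 and .750 at d=.34. The smallest n for two-tailed power .80 is 75 at d=.33, 73 at d=1/3 and 70 at f=.17.

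**Effect detectable at power .80, two-tailed.**

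| n | d | f |
|---|---|---|
| 60 | .368 | .184 |
| 53 | .392 | .196 |
| 52 | .396 | .198 |
| 30 | .529 | .265 |
| 26 | .572 | .286 |

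**Check against the protocol's own second figure.** If the orders are split equally (an assumption), analysis within one order uses 30 subjects. The formula gives a detectable f of .265, and power .786 at f=.26, so the protocol's .26 is about right on the two-tailed, two-level paired reading. Detectable effects scale roughly with 1/√n, so .26 at n=30 implies .26/√2 = .184 at n=60, not .17. The two figures in the paragraph do not agree with each other.

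**Dropout.** 75 × .80 = 60 and 75 × .70 = 52.5. With 52 completers the two-tailed power is .646 at d=.33 and .672 at f=.17. With 53 it is .655 and .681.

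**Type II risk at d=.33.** 1 − .71 = .29 with 60 completers; 1 − .65 = .35 with 52.

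**The case against.** The strongest reply is that the paragraph may have meant a different test. It speaks of repeated measures analyses, and the model described later in the section has two within-subject factors, condition and cocaine dose, hence four cells. If ρ=.5 holds among all four cells and the effect is the same at both doses, the condition main effect averaged over doses has power .94 to .96 with 60 subjects. A four-level F test gives .86 to .89 and a three-level one .80 to .82. None of these supports the stated figure. The averaged main effect and the four-level test do not give .80 either, and the averaged one requires an equal effect in the 0 mg session. No factor has three levels. The conversion of f to d holds only for two levels, and the Experiments section plans the comparison at each dose.

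Other points stand in part:

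- Both effect sizes are given as approximate, and f=.17 is the first one stated. On that figure the shortfall is about 6 points rather than 9. Rounding does not remove it.
- The comparison with f=.26 assumes 30 subjects per order. The protocol randomises order but states no 1:1 split, so this check supports the paired reading without proving it.
- A correlation of .6 would restore .80 at d=.33. The protocol fixes .5.
- The dropout figure is an expectation, 60 is exact at 20%, and the section on anticipated difficulties says that retention has generally not been a problem. But 30% is inside the protocol's own range.
- A null result should be read from its confidence interval rather than from planned power, which limits the practical harm.

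**Conclusion.** The concern holds. On the stated inputs, 60 completers have two-tailed power .71 at d=.33 (.74 at f=.17), and .80 is reached only at d=.37 (f=.18). The stated dropout range leaves 52 to 60 completers. At the lower end, power at d=.33 is .65 and the effect detectable at .80 is d=.40 (f=.20). The .29 to .35 range of type II risk combines two sources: the first 9 points above .20 come from the power statement alone, the rest from 30% dropout.

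The conclusion rests on the two-level paired comparison at each cocaine dose and on ρ=.5, both taken from the protocol. The document does not show how .80 arose. A one-tailed test with 60 subjects and a two-tailed test with 75 both come close to it at d=.33, but the text says two-tailed and 60. If the figure is in fact one-tailed, the protocol's claim to have powered conservatively for two-tailed tests is also wrong.

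The size is moderate: a shift in detectable effect from .33 to .37, or to .40 with heavy dropout. It does not affect the validity of the planned analysis.

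**What to change.** In the power paragraph of Statistical Analysis, state that 60 completers give two-tailed power .80 for d=.37 (f=.18) and .71 for d=.33, and that at 30% dropout (52 completers) power is .80 for d=.40 (f=.20) and .65 for d=.33. Name the contrast to which these figures apply: disulfiram against placebo at one cocaine dose, ρ=.5. For the within-order fallback, state the assumed equal split; f=.26 can stay for 30 per order, with f=.29 for 26 per order.

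In Research Participants, give the yield as 52 to 60 completers.

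The cost is text only, and the stated detectable effect becomes slightly less favourable. No added enrolment is needed if the sponsor accepts these effects. Securing 60 completers at 30% dropout would take 86 entrants (60/.70 = 85.7).

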**LABORATORY MODELS OF COCAINE SELF ADMINISTRATION**

**Study Design Overview**

We propose to investigate effects of disulfiram 250mg compared to placebo on cocaine self-administration using a human laboratory model established by a group at Johns Hopkins ([name]). This investigator has agreed to serve as a consultant for this project, ensuring that the procedures followed are appropriate and that interpretation of the data is consistent with prior studies. Letters from the consultants are included in the appendix

Participants will be admitted to the hospital for 2 study visits. The visits follow the same layout, and participants will receive study drug during one visit and placebo during the other. Participants will be admitted to the hospital and will be randomized to study drug or placebo on the following day. During the next several days staff will familiarize participants with upcoming procedures and participants will complete a mock version study procedures. Participants will remain seated during experimental sessions except for brief visits to the lavatory. The first 30-min of all sessions will be devoted to the collection of baseline data and participant preparation.

At 1pm on days 5 and 7, participants will choose between a dose of cocaine (0mg or 20mg) or a monetary alternative in each of 10 subsequent choices. The same dose of cocaine, 0mg or 20mg, will be available for all 10 choices on a given day and each dose will be assigned to either day 5 or 7 in a randomized, double-blind manner. The monetary alternative will be $.05, $.05, $.05, $.05,$1, $4, $7, $10, $13, or $16 cash, presented in that order. Selections will be made at 15-minute intervals, and participants will receive cocaine doses or cash immediately after indicating their choice, providing vital signs remain within preset intervals. Heart rate variability measures will be conducted throughout the choice session as well.

Study drug will be discontinued on day 7, after completion of the experimental sessions. On day 8, the neurocognitive assessment and continuous heart rate recording will be repeated (as on days 1 and 4), starting at 3:00 PM. Again, subjects will be asked to refrain from smoking tobacco for at least 2 hours before the assessment.

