**Experiments**

We propose assess effects of disulfiram and placebo on cocaine self-administration using an established laboratory model. Each participant will complete the experiment during treatment with placebo and disulfiram. The order in which a participant will receive disulfiram or placebo will be randomized to control for order effects.

At 1pm on days 5 and 7, participants will choose between a dose of cocaine (0mg or 20mg) or a monetary alternative in each of 10 subsequent choices. The same dose of cocaine, 0mg or 20mg, will be available for all 10 choices on a given day and each dose will be assigned to either day 5 or 7 in a randomized, double-blind manner. The monetary alternative will be $.05, $.05, $.05, $.05,$1, $4, $7, $10, $13, or $16 cash, presented in that order. Selections will be made at 15-minute intervals, and participants will receive cocaine doses or cash immediately after indicating their choice, providing vital signs remain within preset intervals. Heart rate variability measures will be conducted throughout the choice session as well.

Study drug will be discontinued on day 7, after completion of the experimental sessions. On days 1, 4 and 8, neurocognitive assessments and continous heart rate recording will be completed starting at 3:00 PM. Subjects will be asked to refrain from smoking tobacco for at least 2 hours before the assessment.

Subjects will be monitored through day 8 and on day 9 they can either go home and return to complete the procedures under the alternate condition (placebo vs. disulfiram), or they can stay in the hospital and start the alternate study drug on the next day.

Day 1 Admit to the CRC, complete neurocognitive testing with continuous heart rate recording.

Day 2 *Randomize to study drug 1. The order in*

which participants *receive disulfiram*

*and placebo will be randomized*

Day 3

Day 4 Neurocognitive testing with continuous heart rate recording.

Day 5 Choice session 1

*Participants will choose between cocaine (0mg or 20mg) and money*

Day 6

Day 7 Choice session 2

*Participants will choose between cocaine (0mg or 20mg, reverse of day 5) and money*

Day 8 Monitor. Neurocognitive assessment with continuous heart rate recording.

Day 9 Discharge or subjects can remain in hospital for study part 2

The total possible dose that a patient can receive during choice sessions is 200mg, and the total dose they can receive over the study visit is 200mg.

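### If an order effect is found, the primary analysis is split by order, where disulfiram versus placebo cannot be separated from visit 1 versus visit 2

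*Protocol*

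**What the plan says.** The trial is a two-visit crossover: "participants will receive study drug during one visit and placebo during the other" (Protocol, Study Design Overview). Its Experiments section gives the reason for two orders: "The order in which a participant will receive disulfiram or placebo will be randomized to control for order effects".

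The Statistical Analysis section first tests for order effects by repeated measures ANOVA, presents that test as a way of establishing equivalence, and expects no difference. It continues: "However, if significant differences are found, then primary analyses will examine effects within each order condition". The power paragraph repeats the rule, "if order effects are detected, then analyses will assess effects within order conditions", and gives the split a detectable effect of its own, f=.26.

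The model is described as follows: "a general linear model will include within-subject factors representing condition (disulfiram vs. placebo) and cocaine dosage". Nothing in the protocol names a visit (period) term or says how the two within-order results would be recombined.

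**The concern.** Randomizing order lets a difference between the first and second admission cancel when the two groups are averaged. The fallback gives up that averaging, and under one reading of its trigger it does so precisely when a visit difference has been detected. What remains are two contrasts of about 30 people each, in which condition and visit are the same variable.

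A visit difference is plausible here because the second admission repeats the same choice procedure in people who have already been through it. The primary conclusion could then show an apparent benefit in one order and an apparent harm in the other with no drug effect at all, or it could hide a real effect in one order. Separately, a non-significant difference test does not establish equivalence, so passing the pre-test does not show what the section says it shows.

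**Working it through.** **Inputs.** From the Protocol: 60 completers ("there will be a dropout rate of 20-30%, yielding a sample size of 60"; 75 × 0.80 = 60, while 30% dropout would leave 75 × 0.70 = 52.5), two-sided alpha .05, power .80, within-subject correlation .5, and f=.26 for the split. Assumed, because not stated: 1:1 allocation to order (30 per order), pre-test level .05, and a visit effect π from 0 to 0.8 SD.

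**The plan's own figure.** For two conditions d = 2f = 2 × .26 = .52. The SD of a within-person difference is √(2(1 − .5)) = 1 SD. With n = 30, two-sided power is 0.786 by the noncentral t and 0.813 by the normal approximation; the exact detectable f is .265. So f=.26 reproduces, and it corresponds to separate tests on about 30 people per order.

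**Confounding.** Let τ be the drug effect and π be visit 2 minus visit 1. The expected disulfiram-minus-placebo difference is

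- disulfiram first: τ − π
- placebo first: τ + π
- average of the two orders: [(τ − π) + (τ + π)]/2 = τ

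Within either order alone, τ and π cannot be separated. Randomizing the cocaine dose to day 5 or day 7 does not help, because both days fall within one visit.

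**What the trigger tests.** The difference between the two groups' drug contrasts is (τ + π) − (τ − π) = 2π, so an order-by-condition test is a test of the visit effect. The order main effect compares totals over both visits. π enters those totals equally in both groups, so that test fires about 5% of the time whatever π is.

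**Size with τ = 0.** Simulated crossovers, 30 per order, correlation .5. After a significant pre-test, significance in either order counts as a finding; otherwise a paired test on all 60 is used.

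| Visit effect (SD) | Each within-order test rejects | Two-stage rate, order-by-condition trigger | Two-stage rate, order-main-effect trigger | Pooled, visit-adjusted test |
|---|---|---|---|---|
| 0 | 5% | 8% | 5% | 5% |
| 0.2 | 18% | 28% | 6% | 5% |
| 0.33 | 42% | 62% | 7% | 5% |
| 0.5 | 75% | 93% | 7.5% | 5% |
| 0.8 | 99% | 100% | 6% | 5% |

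At 0.3 SD the rate with the order-by-condition trigger is about 54%. At 0.5 SD that trigger fires in 97% of trials, and the two orders then almost always point in opposite directions. With the main-effect trigger the split is rarely entered, but once entered it is just as confounded: at least one false rejection in 35%, 66% and 94% of such trials at 0.2, 0.33 and 0.5 SD.

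**Masking.** With τ = −0.33 and π = +0.33, the placebo-first contrast has mean −0.33 + 0.33 = 0 and rejects in 5% of trials, so a real effect disappears there.

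**Power of the alternative.** The pooled visit-adjusted test on 60 people has 71% power at d=.33, and its detectable effect at 80% power is about d=.37, against d=.53 for 30 per order. The gap between 71% and the plan's stated .80 is not a cost of adjustment: the unadjusted paired test on 60 also has 71% power at d=.33 when there is no visit effect.

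**The case against.** Four points can fairly be made for the plan.

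*The trigger is undefined.* If order effect means the order main effect, the overall false-positive rate stays near 5% to 7.5%. This stands. The protocol's description of order effects as being for disulfiram versus placebo fits the order-by-condition reading better, but does not settle it.

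*The decision rule is undefined.* The protocol says effects will be examined within each order, not that one significant order is enough. If both orders must be significant in the same direction after a split, false positives under the order-by-condition trigger fall below 5% (about 1.6% at 0.3 SD and 0.1% at 0.5 SD). This also stands, but power then collapses, to about 2% for d=.33 at a visit effect of 0.5 SD. The split does harm either way.

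*Looking by order has some diagnostic value.* Participants may cross over without a gap: "they can stay in the hospital and start the alternate study drug on the next day". Carry-over is therefore a live meaning of order effect. With carry-over of −0.33 SD into the placebo visit, no drug effect and no visit effect, the disulfiram-first contrast rejects in 41% of trials and the pooled visit-adjusted test in 24%, while the placebo-first contrast stays at 5%. A reader might infer that the split throws away half the sample for nothing, or that adjusting for visit guarantees 5% error in all circumstances. Neither is supported. Equally, carry-over does not rescue the split, because it biases the disulfiram-first contrast directly.

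*The absent visit term may be left to an analysis plan.* This stands as far as it goes. With randomized order the unadjusted pooled test is conservative, with error falling from 5% to about 3% as the visit effect rises to 0.5 SD; only power suffers (71% to 62% at d=.33). The missing term alone would be a minor point. The fallback differs in kind, because it is a rule the protocol states.

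**Conclusion.** The concern holds: the within-order comparison should not be the primary analysis. That conclusion is algebraic and needs no assumed figure. The rule appears twice in the Statistical Analysis section, carries its own power figure, and undoes the purpose the protocol gives for randomizing order.

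The size is conditional. The high rates, from 28% at 0.2 SD to 93% at 0.5 SD, require an order-by-condition trigger, a non-zero visit effect, and a claim based on either order alone. The 8% rate with no visit effect requires the first and last of these. The tempting stronger reading is that false drug effects will result. The documents do not support it, because they give no visit effect, do not say which term is tested, and do not say how two discordant orders would be interpreted.

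**What to change.** In the Statistical Analysis section, delete the order pre-test as a gate, both sentences that move the analysis within orders, the f=.26 contingency, and the claim that the test establishes equivalence.

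Specify one primary model from the start with condition, visit (1 or 2), order, cocaine dose and condition-by-dose. Draw the primary conclusion from the visit-adjusted condition effect pooled over both orders. Report results by order as supportive only. State the absence of carry-over as an assumption of the analysis, since the pooled test holds its 5% error for any visit effect only under that assumption.

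The cost is wording and one or two degrees of freedom; no additional data are needed.
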